## Abstract

**Background:**

*Trypanosoma cruzi* has been divided into Discrete Typing Units I and non-I (II-VI). *T. cruzi* I is predominant in Mexico and Central America, while non-I is predominant in most of South America, including Argentina. Little is known about congenital transmission of *T. cruzi* I. The specific aim of this study is to determine the rate of congenital transmission of *T. cruzi* I compared to non-I.

**Methods/design:**

We are conducting a prospective study to enroll at delivery, 10,000 women in Argentina, 7,500 women in Honduras, and 13,000 women in Mexico. We are measuring transmitted maternal *T. cruzi* antibodies by performing two rapid tests in cord blood (Stat-Pak, Chembio, Medford, New York, and Trypanosoma Detect, InBios, Seattle, Washington). If at least one of the results is positive, we are identifying infants who are congenitally infected by performing parasitological examinations on cord blood and at 4–8 weeks, and serological follow-up at 10 months. Serological confirmation by ELISA (Wiener, Rosario, Argentina) is performed in cord and maternal blood, and at 10 months. We also are performing *T. cruzi* standard PCR, real-time quantitative PCR and genotyping on maternal venous blood and on cord blood, and serological examinations on siblings. Data are managed by a Data Center in Montevideo, Uruguay. Data are entered online at the sites in an OpenClinica data management system, and digital pictures of data forms are sent to the Data Center for quality control. Weekly reports allow for rapid feedback to the sites.

**Trial registration:**

Observational study with ClinicalTrials.gov Identifier NCT01787968

## Background

Chagas’ disease, or American trypanosomiasis, is caused by the protozoan parasite *Trypanosoma cruzi*. It is a major cause of morbidity and mortality in the Americas, and an estimated 9 million persons are currently infected [1]. Of particular concern is the fact that mothers with Chagas’ disease can transmit *T. cruzi* to their fetuses [2].

Mother-to-child transmission of *T. cruzi* has all the characteristics required to be a public health priority, as it is relatively frequent, severe, identifiable, and treatable [3]. In reality, it is a neglected disease and a missed opportunity. Therefore, it is urgent to better understand the epidemiology of mother-to-child transmission and to develop effective prevention programs.

*T. cruzi* has been divided into Discrete Typing Units (DTUs): *T. cruzi* I (TcI) and *T. cruzi* Non-TcI (II-VI). In humans, TcI is predominant in Mexico and Central America, while Non-TcI is predominant in most of South America, including Argentina [4]. In recent studies from Argentina, the risk of congenital transmission has been estimated to vary between 2.6% and 7.9% [5-8]. By contrast, we know very little about the congenital transmission of TcI. It has been suggested that congenital transmission of *T. cruzi* is strain related [2,9], and there is an urgent need to know if TcI transmits differently than Non-TcI. Our primary hypothesis is that congenital transmission rates are different for TcI versus Non-TcI.

*T. cruzi* infected women living in regions where TcI is predominant could differ in terms of risk factors for transmitting *T. cruzi* to their offspring. Low maternal age, low parity, HIV/AIDS, exposure to vectors and high parasitic load have been reported as risk factors for congenital *T. cruzi* infection [9-14]. Family clustering has been observed in Argentina [15], suggesting that some mothers might be predisposed to transmit repeatedly.

There is limited information about the perinatal outcomes of infected infants in low endemicity areas. Congenital *T. cruzi* infection has been associated with premature rupture of the membranes and preterm births, in addition to neonatal complications [14]. Further studies are needed to document the impact of *T. cruzi* infection on perinatal outcomes.

The specific aims of this study are:

– 1. To determine the rate of congenital transmission of TcI compared to Non-TcI;

– 2. To compare the *T. cruzi* infected mothers’ characteristics and exposure to vectors in regions where TcI is predominant and regions where Non-TcI is predominant; and

– 3. To describe the birth outcomes of infected and uninfected infants born to TcI and Non-TcI seropositive women.

## Methods/design

### Overview

We are conducting a prospective study in Mexico, Honduras, and Argentina. We are enrolling women at delivery, collecting umbilical cord blood to measure antibodies of maternal origin, and examining and following up the infants of seropositive mothers and siblings (Figure 1).

**Figure 1 F1:**
[figure not shown]
Study design.

At the time of delivery and as soon as possible thereafter, umbilical cord venous blood is collected for all deliveries during the time periods selected for the study. Written informed consent is obtained immediately after delivery (informed consent during labor and delivery is not ethically acceptable). If the woman declines to participate, the cord blood sample is discarded, and no data are recorded. If the woman accepts to participate, we are measuring transmitted maternal *T. cruzi* antibodies by performing two rapid tests in cord blood (Stat-Pak, Chembio, Medford, New York, and Trypanosoma Detect, InBios, Seattle, Washington). If at least one of the results is positive, we are identifying infants who are congenitally infected by performing parasitological examinations on cord blood and at 4–8 weeks, and serological follow-up at 10 months. Serological confirmation by recombinant ELISA (Wiener, Rosario, Argentina) is performed in cord and maternal blood, and at 10 months. We will perform PCR followed by a qPCR and genotyping on the blood of infected mothers and on the umbilical cord blood.

### Variables

The exposure to TcI will be defined by *T. cruzi* genotyping showing TcI on maternal blood and/or cord blood. In the absence of successful *T. cruzi* genotyping on maternal or cord blood, births occurring in Mexico or Honduras will be considered exposed to TcI.

The exposure to Non-TcI will be defined by *T. cruzi* genotyping showing Non-TcI on maternal blood and/or cord blood. In the absence of successful *T. cruzi* genotyping on maternal or cord blood, births occurring in Argentina will be considered exposed to Non-TcI.

The exposure to both TcI and Non-TcI (co-infection) will be defined by *T. cruzi* genotyping of both TcI and Non-TcI on maternal blood and/or on cord blood, or of TcI on maternal blood and Non-TcI on cord blood, or of Non-TcI on maternal blood and TcI on cord blood.

The primary outcome (Specific Aim 1) will be the congenital *T. cruzi* infection, which will be defined as the presence of one or more of the following criteria:

– Presence of parasites in cord blood (direct parasitological microscopic examination); and/or

– Presence of parasites in infant’s blood at 4–8 weeks (direct parasitological microscopic examination); and/or

– Persistence of *T. cruzi*-specific antibodies at 10 months, as measured by two tests.

A seropositive mother will have at least one positive rapid test on cord blood and a positive ELISA on maternal blood.

The mothers’ characteristics and exposure to vectors variables (Specific Aim 2) that will be collected include:

– Maternal age;

– Parity (including current birth);

– Infected sibling (yes/no) (siblings previously treated for *T. cruzi* infection will be presumed as having been infected);

– Maternal parasitic DNA amount;

– HIV serology (according to tests performed routinely in each country);

– Presence of vectors in the household (Infestation) (yes/no).

– Location in an area with risk of vectorial transmission (yes/no)

The birth outcomes (Specific Aim 3) to be measured are the following:

– Premature rupture of the membranes (PROM), defined as rupture of membranes before admission or before the onset of contractions, whatever the timing of the rupture; [14]

– Gestational age (completed weeks), based on the Last Menstrual Period (LMP) or a clinical estimate (including ultrasound, if available) [16]. In the absence of an ultrasound, the clinical estimate will be based on the Capurro Score [17]. This score is the standard method to evaluate gestational age by physical examination of an infant at birth in Argentina and is widely used in Latin America. The clinical estimate will be used if the discrepancy between the LMP-based estimate and the clinical estimate is greater than 10 days; a preterm birth is <37 weeks;

– Birthweight (grams); a low birthweight baby weighs <2,500 g;

– Head circumference (cm);

– Length (cm);

– Neonatal complications: We will use the definitions of Torrico et al. [14] for the following variables, to be registered at a physical examination of the infant at not later than 24 hours of life:

– Hepatomegaly (when ≥ 2 cm below the right costal margin);

– Splenomegaly (whatever the spleen size under the left costal margin);

– Anasarca (palpebral, genital, or leg edema alone will not be considered);

– Petechiae (whatever their localization);

– Respiratory Distress Syndrome (RDS) will be considered when at least one of the following signs is present: tachypnea, throbbing of the ala nasi, expiratory grunting, intercostal retraction, facial or systemic cyanosis (peripheral cyanosis will not be considered);

– Neurological signs will be classified as present or absent based on tone, level of alertness, Moro and other primary neonatal reflexes, deep tendon reflexes, spontaneous motor activity, pupil diameter (in search of mydriasis or miosis), bulging of fontanelles, and convulsions.

Data about birthweight of siblings and breastfeeding are collected by interviewing the mother at home using the Honduras Demographic and Health Survey (DHS) questions [18]. The DHS is a standardized survey administered around the world, and it includes validated questions and allows for international comparisons [19]. For each newborn and his/her siblings, we will also collect data about blood transfusions, organ transplants, and previous screening and treatment for *T. cruzi*.

Participating hospitals will be collecting data for all women who consent to participate, using the format of the Perinatal Information System of PAHO/WHO already in use in Argentina, Honduras, and Mexico [20]. The variables collected include maternal age, reproductive history, HIV status, LMP, ultrasound examination, PROM, mode of delivery, multiple births, Apgar score at one and five minutes, birthweight, head circumference, and length.

A live birth is a baby born with any sign of life, irrespective of gestational age [16]. A neonatal death is defined as death before 28 complete days of life [16]. An infant death will be defined as death before one year of life [16].

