### Entomological data

Entomological data will be obtained from two different sources to estimate vectorial exposure in the households from seropositive mothers. First, we will use vector distribution and house infestation data from the respective vector surveillance and control programs in Argentina and Honduras, which provide geocoded information and maps on the presence of vectors of different species at the village/locality level. For each household of a seropositive mother, we will thus determine if it is located in a village with or without known house infestation by triatomines using cumulated vector data from the past five years. For the Yucatan Peninsula, Mexico, in the absence of vector control programs, we will use published entomologic risk maps [22]. Based on these maps, households located in villages with low or absent risk will be classified as without house infestation, and households from villages with medium or high risk will be classified as with house infestation.

Second, we will use the community participation method, which was successfully piloted in and previously used in Argentina as well [23]. All of the households from seropositive mothers will be included, corresponding to an estimated 100 households in Mexico, 300 in Honduras, and 200 in Argentina. During the first household visit, information on Chagas’ disease and triatomines will be provided, including photographs and the display of dried specimens of the vector, to ensure that study participants will recognize the vector. Participants will then be instructed to collect any triatomines observed inside (domestic) or outside (peri-domestic) of their homes using a safe procedure and to place them into separate labeled plastic vials or bags. Any insects captured since the time of the initial visit will be gathered during the second visit at 10 months. Triatomine species will be identified by local entomologists from vector control programs in Argentina and Honduras and by entomologist researchers in Mexico, using established entomological keys [24,25].

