### Sample size

We are planning to study 600 mothers with *T. cruzi* infection. The sample size will be achieved by recruiting 13,000 women in Mexico (estimated seroprevalence of 1% in Merida and 0.4% in Valladolid), 7,500 in Honduras (estimated seroprevalence of 4%), and 10,000 in Argentina (estimated seroprevalence of 2%). Based on our pilot study, we estimate that 20% of deliveries will be excluded because the age of the mother will be <18 or because consent is not obtained. In addition, we estimate that 5% of the women will be ineligible because they live outside of the follow-up area in Mexico (which includes the entire Yucatan Peninsula) and that 10% will live outside of the follow-up areas in Honduras and Argentina (which include only each hospital’s department or province).

We estimate that we will recruit 300 mothers with TcI infection and 300 mothers with Non-TcI infection. We will have more than 80% power to detect a difference of 1% transmission for TcI versus 5% for Non-TcI. We estimate that the loss to follow-up will be lower than 10%.

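### Ungenotyped births take their country's strain label and are pooled with genotyped births, and no listed analysis shows how far the primary TcI versus Non-TcI contrast depends on that rule

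*Protocol article*

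**What the plan says.** The hypothesis is about strain: "Our primary hypothesis is that congenital transmission rates are different for TcI versus Non-TcI" (Background). Under Variables, exposure is set by genotyping of maternal and/or cord blood. Without a successful genotype, "births occurring in Mexico or Honduras will be considered exposed to TcI" and "births occurring in Argentina will be considered exposed to Non-TcI". The Background gives the basis for this rule: "TcI is predominant in Mexico and Central America, while Non-TcI is predominant in most of South America, including Argentina". It gives no percentage, and the article states neither an expected genotyping success rate nor how often genotype and region agree.

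The Analysis plan compares transmission by this exposure with exact binomial tests. It also lists:
- separate analysis of co-infection and of maternal HIV/AIDS;
- a restricted re-analysis aimed at non-congenital routes of infection;
- stratification by breastfeeding;
- adjustment for maternal age, parity, household vectors, maternal parasitic DNA amount, mode of delivery and infected sibling.

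Genotyping status, country and site appear in none of these.

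For power, the Sample size section states "We estimate that we will recruit 300 mothers with TcI infection and 300 mothers with Non-TcI infection" and "We will have more than 80% power to detect a difference of 1% transmission for TcI versus 5% for Non-TcI".

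**The concern.** A label inferred from country carries the same weight as an observed genotype. Where the inference is wrong, a birth with one strain is counted under the other. If errors are unrelated to outcome, the two rates move towards each other and power falls.

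The errors may also be related to outcome. Genotyping needs detectable parasite DNA (Blood samples and laboratory evaluations), high parasitic load is cited in the Background as a risk factor for transmission, and a cord-blood genotype is plausibly easier to obtain when the infant is infected. Off-type transmitters would then be moved to their true group more often than off-type non-transmitters, and the bias need not be towards no difference.

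At stake is whether the primary result can be read as a statement about strain, and whether a reader can see how much of it rests on inferred labels.

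**Working it through.** **Inputs from the article:** 1% versus 5%, and 300 mothers per group (Sample size). **Assumed:** two-sided alpha 0.05, Fisher's exact test as the exact comparison, and every mislabelling share and genotyping rate below.

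**1. The plan's own figure.** At 300 per group, the pooled normal approximation gives 82.1%, which reproduces the stated power above 80%. Fisher's test, by enumeration, gives 79.8%. Both require every label to be right.

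**2. Dilution.** Let m be the share of all births in each group with the wrong label, unrelated to outcome. The apparent rates are

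p1' = 0.01(1 − m) + 0.05m and p2' = 0.05(1 − m) + 0.01m.

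For m = 10%: p1' = 0.009 + 0.005 = 1.4% and p2' = 0.045 + 0.001 = 4.6%.

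| m (assumed) | Apparent rates | Fisher power, 300/300 |
|---|---|---|
| 0 | 1.00% vs 5.00% | 79.8% |
| 1% | 1.04% vs 4.96% | 77.7% |
| 2% | 1.08% vs 4.92% | 75.6% |
| 5% | 1.20% vs 4.80% | 68.9% |
| 10% | 1.40% vs 4.60% | 56.6% |

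Here m = u × w, where u is the share ungenotyped and w the share of inferred labels that are wrong. If half are ungenotyped, m = 1% needs w = 2%, and m = 10% needs w = 20%.

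**3. Outcome-dependent labelling (illustration, all strain and genotyping figures assumed).** Take 400 mothers in Mexico and Honduras and 200 in Argentina, as in the household counts under Entomological data. Let the true rate be 4% for both strains, with 25% off-type in Mexico and Honduras and none in Argentina, and genotyping success of 90% in transmitters and 30% in non-transmitters.
- Labelled TcI: transmitters 12 + 4 × 0.1 = 12.4; non-transmitters 288 + 96 × 0.7 = 355.2; rate 12.4/367.6 = 3.4%.
- Labelled Non-TcI: transmitters 8 + 4 × 0.9 = 11.6; non-transmitters 192 + 96 × 0.3 = 220.8; rate 11.6/232.4 = 5.0%.

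A difference appears where none exists. With 10% off-type instead of 25%, the rates are 3.8% and 4.4%. With equal genotyping success in both outcomes, both stay at 4.0%.

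**4. What a genotyped-only comparison can and cannot show.** It removes inferred labels but loses size. For 1% versus 5%, Fisher power is 59.2% if 70% are genotyped (210 per group), 39.6% at 50% (150) and 15.2% at 30% (90).

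It does not separate strain from country. Suppose a pure country effect of 1% versus 5%, no strain effect, and 180 and 90 genotyped births (assumed: half of 400 and 200 after 10% loss). The genotyped-only rates then point the same way in about 95% of studies.

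**The case against.** The fallback rule is open and fixed in advance, and it has a rationale. Dropping ungenotyped mothers would select on parasitic load, itself a risk factor, and would cost power. That stands, and it is why the region-assigned comparison should remain the main analysis.

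A full protocol or SAP, not shown, may hold sensitivity analyses. The point therefore rests on what the article states: an exposure rule that can mislabel, together with a detailed list of re-analyses, none of which tests it.

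Three stronger readings are tempting and not supported:
- **That differences in vectors, care and test performance would simply be read as strain differences.** Household vectors and mode of delivery are adjustment variables, the second-step analysis excludes certain vector-exposed infants, Aim 2 compares mothers by region, and the Stat-Pak was validated on cord blood in all three countries. Residual country confounding is possible but not shown.
- **That power will fall to some particular value.** No figure in the article fixes the mislabelled share, and 10% of all births is a heavy assumption.
- **That 100 of 400 mothers in Mexico and Honduras are expected to be Non-TcI.** A reader might infer this from "corresponding to an estimated 100 households in Mexico, 300 in Honduras, and 200 in Argentina" set against the planned 300 and 300. The article does not say so, and the two sets of figures may simply disagree.

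**Conclusion.** The concern holds as one about misclassification. Inferred and observed strain labels are pooled in the primary comparison, on a basis described only as predominance, and no listed analysis shows the result by genotyping status or country. The planned power has little room: under the assumptions above, Fisher power runs from 79.8% with perfect labels to 75.6% at 2% and 56.6% at 10% mislabelled. These are illustrations, not forecasts. If labelling depends on infant infection, the direction of bias is also open.

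It does not follow that genotyping more births would settle whether strain or country explains a difference. Confirmed strain remains nearly collinear with country wherever one group predominates, so agreement in direction between the genotyped-only and region-assigned results is no evidence for strain over country. Only strain contrasts within a country bear on that.

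**What to change.** 1. Keep the region-assigned comparison as the main analysis.
2. Prespecify, as a supporting analysis, the same exact comparison restricted to births with a successful maternal genotype. Using maternal rather than cord genotypes limits the dependence of labelling on infant infection.
3. Report the share genotyped in each country.
4. Tabulate transmission separately for Mexico, Honduras and Argentina and, where off-type births exist, by strain within country.
5. Unless within-country contrasts support a strain effect, describe the result as a difference between regions where TcI or Non-TcI predominates.

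The cost is a little analysis on data already planned, since maternal genotyping is in the protocol. The drawback is that the genotyped subset is smaller and over-represents mothers with higher parasitic load, and within-country off-type numbers may be few. These analyses support the main result and do not replace it.

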A confirmatory ELISA will be performed for all 10-month follow-up tests that are positive or in question. The samples will be sent to Tulane University. Serologic analysis will be performed according to the manufacturer protocol using the FDA-cleared Hemagen Chagas Kit (Hemagen Diagnostics, Inc., Columbia, Maryland), a qualitative ELISA designed for the detection of circulating antibodies to *T. cruzi* in serum and plasma.

Congenital infection with *T. cruzi* is sought for by direct microscopic examination of blood buffy coat collected in six centrifuged microhematocrit heparinized tubes as previously described [2,14,38,39]. In those cases in which it is not possible to collect enough blood to fill 6 capillary tubes, collecting blood to fill at least one capillary tube will be considered acceptable. The detection limit of such parasitological detection was estimated to be 40 parasites/ml (p/ml) [38,39], which allowed the detection of more than 90% of the congenital cases in Bolivian endemic areas [40]. The number of positive microhematocrit tubes containing parasites, as well as the number of detected parasites per tube, allowed estimation of parasitemia as either low (≥ 40 p/ml - < 150 p/ml), medium (≥ 150 p/ml - ≤ 400 p/ml), or high (> 400 p/ml). Positive parasitological examinations will be filmed when possible. The films will be downloaded to the Chagas study webpage and shared between the study sites.

We will perform molecular tests to estimate the parasitic DNA amount (PCR followed by a qPCR in positive cases) and to identify the *T. cruzi* genotype (TcI and/or Non-TcI) on the blood of infected mothers. We will also perform PCR followed by genotyping on the umbilical cord blood samples. An international consensus has recognized direct parasitological examinations of cord or neonatal blood collected in capillary tubes, as well as serological investigations of infant blood at 10 months of age, as the best tools for the biological diagnosis of *T. cruzi* congenital infection, whereas PCR must still be standardized and validated for such use [2]. Thus, the research team is using blood parasitological examinations and late serology to identify infected newborns. PCR will not be used for diagnostic purposes, but it will aid in verifying the presence of parasitic DNA in samples before they are quantified via qPCR or before genotyping.

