### Analysis plan

We will compute the rate of congenital transmission among seropositive mothers according to the exposure to TcI or Non-TcI with the corresponding confidence intervals and compare them using binomial exact tests. A seropositive mother will have at least one positive rapid test on cord blood and a positive ELISA on maternal blood. Cases with TcI/Non-TcI co-infection and with maternal HIV/AIDS will be analyzed separately, and transmission rates will be compared to the rest of the population.

In a second step, we will repeat the analysis after excluding infants with negative parasitological examinations and negative PCR on cord blood, and with a history of transfusion and/or organ transplant, and/or who are living in households exposed to the vector (presence of vectors and/or location in an area at risk of vector transmission). The resulting congenital transmission rate will be a more conservative estimate, which will be less likely to be biased by non-congenital routes of transmission. We will also stratify according to breastfeeding (yes/no), another potential route of neonatal transmission.

We will adjust the comparison of TcI/Non-TcI transmission rates for potential confounders:

– Maternal age at delivery (in five-year categories);

– Parity (primiparae/multiparae);

– Presence of vectors in the household (yes/no);

– Maternal parasitic DNA amount;

– Mode of delivery (C. section vs. vaginal); and

– Infected sibling (yes/no) (siblings previously treated for *T. cruzi* infection will be presumed as having been infected).

Mantel-Haenszel chi-square tests will be used for stratified analyses, which will take one categorical factor into account at a time. A logistic regression will be also performed and will include all potential confounders. Adjusted odds ratios (OR) and confidence intervals will be estimated.

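### Co-infection is labelled partly from cord-blood genotype, which is obtained mostly when parasites were transmitted, so the comparison of co-infected cases with the rest is biased upward

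*Protocol article*

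**What the plan says.** The Variables section defines exposure to TcI by "genotyping showing TcI on maternal blood and/or cord blood" and exposure to Non-TcI by "genotyping showing Non-TcI on maternal blood and/or cord blood". Co-infection is assigned when both types are found in maternal and/or cord blood, and also when the two samples disagree: "or of TcI on maternal blood and Non-TcI on cord blood, or of Non-TcI on maternal blood and TcI on cord blood".

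If neither sample can be typed, the country decides: "births occurring in Mexico or Honduras will be considered exposed to TcI", and "births occurring in Argentina will be considered exposed to Non-TcI". A cord genotype can therefore override the country default when the mother could not be typed.

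On cord blood, the section on blood samples and laboratory evaluations says: "We will also perform PCR followed by genotyping on the umbilical cord blood samples". It adds that PCR is there to confirm parasite DNA in a sample before quantification or genotyping, and is not used for diagnosis. The first criterion of the primary outcome is parasites seen by microscopy in cord blood.

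The Analysis plan uses the label as follows: "Cases with TcI/Non-TcI co-infection and with maternal HIV/AIDS will be analyzed separately, and transmission rates will be compared to the rest of the population". The article describes no maternal-only classification, either as the main definition or as a sensitivity analysis.

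**The concern.** An exposure should be determined in the same way whether or not the outcome occurs. Here a mother-infant pair with transmission has two samples that can reveal a second type. A pair without transmission has, in practice, one. Two routes to the co-infection label (disagreement between mother and cord, and both types in cord blood alone) are therefore open mainly to transmitting pairs. Births labelled co-infected will be enriched for infected infants by construction, and recruiting more women does not remove this. A real effect of co-infection could not be told apart from an effect of the labelling rule.

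The country default brings a milder form of the same problem into the main contrast. An untyped Argentine mother who carries TcI moves to the TcI group if her infant's cord blood is typed, and otherwise stays in Non-TcI.

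**Working it through.** **Plan figures.** The protocol gives no figure for co-infection, typing success or mother-cord disagreement. Its power statement (300 per group, 1% versus 5%, more than 80%) gives 82.1% by a pooled z-test and 79.8% by Fisher's exact test, two-sided 5% assumed. The labelling rule does not enter that calculation. The useful planning figures are the expected events: 1% × 300 = 3 and 5% × 300 = 15.

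**Check 1: transmission rate among births labelled co-infected.** True transmission t is set equal for everyone, so any excess is bias. All other inputs are assumptions, applied to truly co-infected mothers:
- b: probability that maternal blood alone shows both types
- s: probability that maternal blood shows one type
- q, f: cord typing success in infected and uninfected births
- o = 0.4: a typed cord shows only the other type
- d = 0.2: a typed cord shows both

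Formulas:
- A = s(o + d) + (1 − b − s)d
- P(label | infected) = b + qA
- P(label | uninfected) = b + fA
- Labelled rate = t(b + qA) / [t(b + qA) + (1 − t)(b + fA)]

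Worked example with t = 5%, b = 0.2, s = 0.4, q = 0.8, f = 0: A = 0.24 + 0.08 = 0.32, and P(label | infected) = 0.2 + 0.256 = 0.456. The rate is 0.0228 / (0.0228 + 0.19) = 10.7%.

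| b | s | q | f | Labelled rate (truth 5%) |
|---|---|---|---|---|
| 0.1 | 0.4 | 0.8 | 0 | 16.4% |
| 0.2 | 0.4 | 0.8 | 0 | 10.7% |
| 0.2 | 0.4 | 0.8 | 0.05 | 10.0% |
| 0.4 | 0.4 | 0.8 | 0 | 7.6% |
| 0.8 | 0.15 | 0.5 | 0.05 | 5.3% |

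Over the whole grid (t of 1% or 5%, b from 0.1 to 0.8, q from 0.5 to 0.8, f from 0 to 0.05) the ratio to the true rate runs from 1.05 to 3.62. With a maternal-only label, q and f drop out and the ratio is 1.00, provided maternal typing success is unrelated to transmission.

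**Check 2: a simpler model, including the comparison group.** Assume 10% of mothers are truly co-infected. Maternal typing finds the second type with probability gm, and cord typing finds it in infected infants with probability gc. Detection is 1 − (1 − gm)(1 − gc) in cases and gm in non-cases.
- gm = 0.2, gc = 0.6: detection in cases 0.68; rate 0.034 / (0.034 + 0.19) = 15.2%; the rest read (0.05 − 0.0034) / (1 − 0.0224) = 4.8%.
- gm = 0.6, gc = 0.3: detection in cases 0.72; rate 0.036 / (0.036 + 0.57) = 5.9%; the rest read 4.9%.

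If 20% are co-infected, the rest fall to 4.5% at worst.

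**Check 3: main contrast through the country default.** Assume 300 mothers in Argentina and 300 elsewhere, 5% transmission throughout, q = 0.8 and f = 0. A share of Argentine mothers carries TcI and nobody elsewhere is discordant. Maternal typing succeeds with probability m.
- Share 5%, m = 0.2: 15 mothers, 0.75 infected. Relabelled: 0.75 × 0.84 = 0.63 infected and 14.25 × 0.2 = 2.85 uninfected. TcI = 15.63 / 303.48 = 5.15%; Non-TcI = 14.37 / 296.52 = 4.85%.
- Share 20%, m = 0.8: 5.13% and 4.82%.
- Share 20%, m = 0.2: 17.52 / 313.92 = 5.6% and 12.48 / 286.08 = 4.4%.

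Under maternal-only labelling both rates are 5.0% in each scenario. If discordance is the same in both regions, the shifts cancel.

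**The case against.** Four objections carry weight.

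**Cord DNA is not the outcome.** A reader might infer that a cord genotype exists only when the infant is infected. The protocol does not say so. PCR is described as not yet validated for diagnosis, and the outcome rests on microscopy and 10-month serology. The Analysis plan also foresees infants with negative parasitology and negative cord PCR. The link is strong but not an identity. Allowing 5% cord typing success in uninfected births reduces the bias without removing it. The direction needs only that typing succeeds more often in infected births.

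**A threefold excess is not an estimate.** A reader might take the upper figures as the expected error. They are the worst corner of assumed inputs, and if maternal blood usually shows both types the inflation is about 5%. Absolute numbers are also small. With 600 mothers, 10% co-infected, gm = 0.2 and gc = 0.6, about 600 × 0.1 × 0.224 = 13 mothers are labelled, with about 2 infected infants against 0.7 expected. The exact 95% interval for 2 of 13 runs from 1.9% to 45.4%. This limits what the comparison can show, but does not make a biased comparison acceptable.

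**The primary result is not shown to be compromised.** The co-infection comparison is not a specific aim and plays no part in the sample size. The main contrast moves noticeably only if discordance with the country default is common and one-sided and maternal typing often fails.

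**A maternal-only label has its own flaws.** High parasitic load is listed in the Background as a risk factor for transmission, and typing needs parasite DNA, so maternal typing success may also track the outcome. With about 3 and 15 expected events, replacing a known cord genotype by a geographic default is also a real loss. This is why the maternal-only definition should stand beside the combined one in the main contrast and not replace it.

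**Conclusion.** The concern holds for the comparison of co-infected cases with the rest. As written, the labelling rule inflates the co-infected transmission rate whenever cord typing succeeds more often in infected than in uninfected births. The direction follows from the protocol's own definitions. The size does not: with a true rate of 5%, assumed inputs give about 5% to 16%, driven mainly by how often maternal blood alone shows both types.

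For TcI versus Non-TcI the effect is usually about 0.1 to 0.2 percentage points on each rate. It reaches 5.6% versus 4.4% only in the extreme scenario of Check 3, and the documents do not show that this scenario applies. Check 3 assumes no true difference between the types. The point should be corrected, but it does not invalidate the primary analysis.

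**What to change.** 1. For the co-infection comparison, define co-infection from maternal-blood genotype only. Report cord genotype descriptively, as mother-infant concordance among pairs with both samples typed.
2. For TcI versus Non-TcI, report a maternal-only definition (with the country default where the mother cannot be typed) beside the combined definition, and state whether the conclusion changes. With so few events this is worth doing even though the expected shift is small. At 3/300 versus 15/300 Fisher's p is 0.007; if two cases move between groups, 5/302 versus 13/298, it is 0.058. This is an illustration only, and such moves may be correct for the individual pairs.
3. Report typing success in maternal and in cord blood by infection status, so that a reader can judge the remaining dependence.

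**Cost.** The change is one of wording plus one additional tabulation, with the same samples and assays. A few pairs typed only on cord blood revert to the country default in the maternal-only analysis. Maternal-only labelling removes the dependence built into the definition, but not any that arises because maternal parasite load affects both typing success and transmission.
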